#### Waitlist condition

Participants in the waitlist condition do not receive access to the ST-informed modules. They continue to use the general features of the 7 Cups platform (e.g., chat rooms, peer-support, standard listener responses, and forums) without receiving the specific ST-informed self-help or training material. To reduce contamination, active-condition participants are instructed not to share the material in any of the public or group spaces. These spaces are monitored and in any cases that links, exercises, or content is shared, the 7 Cups head of research (HOR) and their team removes them. Waitlist participants are granted full access to the ST-informed modules only after completion of the final (t2) assessment or upon withdrawal from the study (if they wish to access it after withdrawal).

Participants are sent reminders to encourage them to continue and complete the intervention and assessments every two weeks and the post assessment after 4 weeks. Adherence rates are measured and shall be included in the analysis as an indicator of the feasibility of the intervention. Participants in our study are free to use any concomitant support or interventions on the 7 Cups platform or elsewhere. Waitlist participants continue their usual use of 7 Cups, without any access to ST-informed intervention content during the waitlist phase. Waitlist participants are requested to report the use of any other growth paths on 7 Cups in the post assessment. Both conditions use 7 Cups as normal, but the active conditions have access to the ST-informed learning content that is not available elsewhere on the 7 Cups website.

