### Methods, assignment of interventions

#### Allocation

The gold standard of double blinding is not applicable here due to the nature of the intervention, as participants inherently know which condition they are assigned to. Regarding the study team, there are two parts: one within 7 Cups (HOR) and one outside. The HOR team has access to participants, can allocate them, and send messages and links based on their assigned condition. The 7 Cups HOR compiles a list of all members and another list of all listeners who respond to the invitation, provide consent, and complete the UIC. These lists are securely stored on the 7 Cups server and only accessible to the 7 Cups HOR. The 7 Cups HOR provides these two lists of UICs, one for members and one for listeners, to the external team. The external team generates a randomization sequence using unique participant codes and passes this list to the HOR team. Thus, the external team has no immediate knowledge of allocation, and although the HOR team needs to know for procedural aspects, they are blinded to the randomization process. We utilise a random sequence generator to assign member and listener participants to the growth path or waitlist condition and the listener training or waitlist, respectively. The allocation sequence is generated using a computer-based tool provided by Sealed Envelope Ltd. This tool, titled “Create a blocked randomisation list,” was accessed online on August 29, 2023. The sequence was created with a seed of 21 for the list of members and seed of 23 for the list of listeners, and block sizes were set at 50, 100, 150, and 200, resulting in a total list size of 200 for members and 200 for listeners. This method reduces sequence predictability for the 7 Cups HOR who has direct contact with participants. The lists of assigned UICs are sent to the 7 Cups HOR, who messages participants links to either the growth path or waitlist assessments, and listener participants to either the listener training or waitlist assessments, as appropriate. Participants in the member and listener waitlist conditions do not receive any intervention until the waitlist assessments are completed. Upon completion of the assessments, waitlist participants are sent the links to the growth path or listener training for the waitlist members and listeners, respectively. A subsample of participant pairs is selected with each pair consisting of 1 listener and 1 member. The listeners have completed the ST-informed listener training and support their assigned member who is working through the OSI using the chat/messaging system on 7 Cups. For data analysis, the statistician is outside 7 Cups and unaware of allocation issues. The dataset includes allocation information for analysis, but the final data analysis will be performed on a coded dataset once data collection is complete. Regarding assessor bias, our assessments are conducted fully digitally and online without direct human involvement, eliminating the risk of assessor bias. For qualitative analysis, there may be a risk of bias if raters know about allocation. Therefore, we will have independent raters who are unaware of participants’ allocation. This approach is adopted to ensure the integrity and transparency of the study while acknowledging the limitations posed by the online setting.

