
### Data collection, management and analysis

The study employs a pre-post-follow-up design for the assessments. These assessments are facilitated through LimeSurvey, a General Data Protection Regulations (GDPR) compliant tool. The links for the t0 pre-assessment are sent to participants after being assigned to their respective conditions by the 7 Cups HOR. Our research team and the 7 Cups HOR monitor the progress of the participants and send them a link to complete the t1 post-assessment survey upon completion of the growth path, listener training, or 4 weeks into the waitlist condition. Participants who stop progressing on the growth path, listener training, or assessments for more than a week are sent reminders by the 7 Cups HOR. A link for the t2 follow-up assessment is sent two weeks after the completion of the t1 assessment. After completing the t2 assessment, the member and listener waitlist participants are sent the link to the growth path or listener training, respectively. If participants want to opt out of the study or request their assessment data to be deleted, they are instructed to contact the 7 Cups HOR or the Data Protection Officer at the IPU. After data cleaning, all participant UICs will be deleted, resulting in a fully anonymized dataset for further analysis.

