### Monitoring

The Principal Investigator (PI) assumes responsibility for several key aspects of the study. The PI is in charge of any interim analyses and stopping guidelines, maintaining exclusive access to these interim results and making the final decision to terminate the trial. The PI also establishes plans for collecting, assessing, reporting, and managing solicited and spontaneously reported adverse events and other unintended effects of the intervention or participation. This approach upholds the integrity and transparency of the study while acknowledging the responsibilities of the PI.

This study does not include a formal, dedicated measure of adverse events. However, in line with 7 Cups safety protocols, any participant presenting signs of self-harm risk or crisis is escalated to crisis resources and local emergency services if needed. The PI monitors all communications from the 7 Cups Head of Research (HOR) related to adverse events. If serious adverse events occur, they are documented and reviewed as part of the ethical oversight.

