### Ethics

In terms of ethics and dissemination, the study is designed with a strong emphasis on ethical considerations and transparency. Although no formal Data Monitoring Committee was established due to the low-risk nature of the intervention, provisions are in place for the premature termination of the study under specific circumstances, such as insufficient participant recruitment, significant changes in 7 Cups practices, or early evidence of harm or benefit from the growth path or listener training. Training was completed by all authorised personnel who are involved in the study to ensure responsibilities, and protocols are clear and understood. Despite the minimal anticipated risk, the study thoroughly assesses any potential harm. Serious Adverse Events (SAEs) that occur during the study, including those related to suicide attempts or completed suicide, are continuously monitored and responded to by 7 Cups. Internal audits are carried out to verify all procedures, including recruitment, consent, enrolment, and data collection.

Data confidentiality and secure coding are prioritised. Participants’ data are only accessible to authorised personnel and securely stored. The complete dataset, once finalised, will be transferred to the principal investigator, with limited access granted to other IPU members for analysis.

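### The Ethics section claims thorough harm assessment and continuous SAE monitoring, which the procedures in Monitoring and Table 1 cannot support; the claim should be limited to events that become known

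*Protocol article*

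**What the plan says.** The Ethics section makes two strong statements. It says that "the study thoroughly assesses any potential harm", and that SAEs, "including those related to suicide attempts or completed suicide, are continuously monitored and responded to by 7 Cups". It also lists early evidence of harm among the grounds for ending the study prematurely, with no data monitoring committee.

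The Monitoring section describes the procedures. It says: "This study does not include a formal, dedicated measure of adverse events". Two concrete routes follow. First, "any participant presenting signs of self-harm risk or crisis is escalated to crisis resources and local emergency services if needed". Second, "The PI monitors all communications from the 7 Cups Head of Research (HOR) related to adverse events". The section also makes the PI responsible for plans covering solicited as well as spontaneous reports, but names no tool for soliciting them.

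Four other places bear on the point:

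- Table 1 (Outcomes) lists no adverse-event or suicidality instrument at any time point.
- Data collection, management and analysis gives the response to silence: "Participants who stop progressing on the growth path, listener training, or assessments for more than a week are sent reminders by the 7 Cups HOR".
- Allocation says that, for a subsample of pairs, trained listeners "support their assigned member who is working through the OSI using the chat/messaging system on 7 Cups".
- Waitlist condition says: "Waitlist participants are granted full access to the ST-informed modules only after completion of the final (t2) assessment", or on withdrawal for those who wish it. No assessment follows t2.

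**The concern.** The claim and the described procedures do not match. The setting is a worldwide online platform, and the article describes no contact with participants, relatives or care providers outside it. A suicide attempt, hospital admission or death away from the platform need not show any sign there and need not generate a message. In the study's data it would be a participant who stopped responding. That participant would be sent a reminder and, under Statistical methods, would count as lost to follow-up, a category that the article does not split by cause.

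Two things are at stake. A report of no SAEs would carry the weight of continuous monitoring without having earned it. The stopping ground for early evidence of harm would also rest on the same incomplete information. This matters in this population: members are described as often distressed, absence of crisis is self-confirmed at sign-up, and the only stated exclusion is refusal of consent to data use.

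**Working it through.** **1. The sections side by side**

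| Question | Ethics | Monitoring, Table 1 and data collection |
|---|---|---|
| How is harm assessed? | Thoroughly | No dedicated measure; no item in Table 1 |
| Which SAEs are followed? | Those occurring during the study, completed suicide included | Those shown by visible signs or communicated by the HOR |
| What happens on silence? | Not addressed | Reminder, then loss to follow-up |

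The described routes cover events that become visible or are reported. The claim covers all SAEs.

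**2. Inputs**

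From Sample size: four groups of 50 and potential attrition of 25%. The total reproduces: 4 × 50 = 200, of whom 100 are in the active groups and 100 on the waitlists. The article gives no SAE rate, detection probability or waitlist uptake, so these are assumptions below.

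**3. Silence**

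At 25% attrition, 200 × 0.25 = 50 participants are lost to the surveys (12.5 per group). If one to five of these losses were caused by an SAE, they would be 1/50 = 2% to 5/50 = 10% of the losses. Nothing described would separate them from ordinary dropout. The figure of 50 is a ceiling for unknown safety status at that attrition, since someone who stops answering surveys may still log in.

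**4. What a zero count would support**

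One-sided 95% upper bound on risk with zero recorded events: (1 − 0.05^(1/n)) / d, where d is the assumed probability that an event is detected.

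| n | d = 1 | d = 0.75 | d = 0.50 | d = 0.25 |
|---|---|---|---|---|
| 100 (both active groups) | 3.0% | 3.9% | 5.9% | 11.8% |
| 50 (one group) | 5.8% | 7.8% | 11.6% | 23.3% |

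Chance of recording at least one SAE among 100 at a true risk of 1%: 1 − (1 − 0.01d)^100. This is 63% at d = 1, 39% at d = 0.50 and 22% at d = 0.25.

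**5. Possible difference between groups**

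Active participants have programme progress tracked, a subsample of self-help members has an assigned listener, and the HOR knows the allocation. If detection were 75% in active and 50% in waitlist groups, equal true risk would appear as a ratio of 0.75/0.50 = 1.5. Reversed, it would be 0.50/0.75 = 0.67, and equal detection gives 1.0. The documents do not say which applies.

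**6. Exposure after the last assessment**

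If W waitlist participants start the programme, the share of all starts that come late is W / (100 + W).

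- All 100 start: 100/200 = 50%.
- 25% lost, all others start: 75/175 = 43%.
- 25% lost, half of the others start: 37.5/137.5 = 27%.
- None start: 0%.

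**The case against.** The strongest defence has four parts.

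- **Disclosure.** The absence of an adverse-event measure is stated openly, and the PI is to plan for solicited reports, so a fuller procedure may exist elsewhere. This limits what can be said about conduct. It does not make the two sections agree, and Dissemination plans presents the article as public access to the full protocol.
- **Equal platform use.** A reader might infer that waitlist participants have little beyond survey links, and so that detection certainly differs by arm. The documents do not support that. Waitlist condition gives them the platform's general features and says that both conditions use it as normal. Escalation applies to any participant, and reminders also cover stalled assessments. A difference is possible, with unknown size and direction.
- **Waitlist design.** Access after the final assessment is how a waitlist normally works, and nothing says that platform safeguarding ends at t2. A reader might infer that half of all exposure goes unobserved. Half is the ceiling, and what is missing after t2 is study assessment, not necessarily platform oversight.
- **No planned safety comparison.** The article plans no SAE rate and no between-arm SAE test; it says only that SAEs are documented and reviewed. This stands. The bounds above therefore illustrate what a zero count could bear and do not correct a planned analysis.

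Nor do the documents say that the HOR selects which events reach the PI. They say only that the PI relies on the HOR's communications.

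**Conclusion.** The claim is wrong as written. Ethics asserts thorough harm assessment and continuous monitoring of SAEs. Monitoring, Table 1 and the handling of non-response describe a route that reaches only events that become visible or are reported. A zero count would support neither the claim nor the absence of early evidence of harm.

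The size depends on the detection probability, which the article does not give. For 100 active participants with no recorded events, the upper bound runs from 3.0% at complete detection to 11.8% at 25% detection. At the planned attrition, up to 50 of 200 participants could end with unknown status. Up to half of programme starts follow the last assessment (43% at 25% attrition with full waitlist uptake, fewer otherwise). Differential ascertainment by group is a plausible risk, not a documented fact. The contradiction between the sections depends on none of these assumptions.

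**What to change.** - **Wording.** Reconcile Ethics with Monitoring by limiting the claim to SAEs that come to the attention of the platform or the study team, and withdraw the statement that harm is thoroughly assessed.
- **Ascertainment.** Keep the ongoing HOR-to-PI communication. In addition, where consent and platform records allow, have 7 Cups check safeguarding escalations and last login in the same way for all four groups over the same period. Recent login is already an eligibility criterion. Do this before the participant codes are deleted after data cleaning, because the link is lost then.
- **Reporting.** Give SAEs by group. Show participants with neither a login nor a survey response as status unknown, not as event-free. State that off-platform events and waitlist exposure after t2 are not captured by study assessments.

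The record check cannot detect off-platform events. It only separates people still active on the platform from those about whom nothing is known, so the narrower wording is needed in any case. If the link has already been lost, the wording and the stated limits still apply.

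The cost is a less favourable safety statement and a small data extract. No new visits or questionnaires are needed.

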### Dissemination plans

We intend to publish the key results of the study followed by publications focusing on selected aspects of the study in international peer-reviewed journals. Furthermore, we intend to communicate key results to the public via the 7 Cups platform following data analyses. Public access to the full protocol is provided by this manuscript. Public access to participant-level datasets is not intended. Access to statistical codes is intended to be provided on request. This protocol was written following the SPIRIT protocol guidance.

## Discussion

Despite the great need for mental health interventions, there is limited research available showing the efficacy of digitally delivered ST-informed interventions [54]. This study represents an exploratory RCT that primarily aims to assess feasibility and gather preliminary efficacy data regarding digitally delivered ST-informed interventions. This study additionally aims to explore the challenges, and user experience of novel, digital interventions on a widely accessible platform (7 Cups). By investigating a digital self-help and paraprofessional program informed by systemic therapy principles, this study aims to take a step towards enhancing global mental health support. Our aim in investigating paraprofessionals’ outcomes is to assess whether learning ST-informed techniques may benefit listeners’ mental health. A broader question—whether this guidance also improves member outcomes beyond unguided OSI—would require a separate design. Future research with larger samples is encouraged to address how paraprofessional guidance modifies member outcomes relative to purely self-guided interventions. We hypothesize that intervention group members will show greater reductions in mental health distress compared to control groups. The strengths of this research include its theory-based intervention and consideration of multiple covariates. A potential limitation is that participants with very low baseline distress may not demonstrate measurable change on the K6 or other symptom-based measures. Future research might include dedicated measures of positive wellbeing or functioning to better capture change in subclinical populations. The findings may contribute to discussions on digital mental health strategies to alleviate psychological distress on a large scale that overcomes common barriers to mental health interventions such as cost. This project is an exploratory approach to evaluate feasibility and preliminary efficacy. Claims about long-term effectiveness are beyond its scope, and larger-scale trials would be necessary to confirm or refute efficacy on a broader scale. While this study is exploratory and not fully powered, it may serve as a starting point to shape larger, more definitive evaluations. It could also contribute to the ongoing dialogue about how digital mental health interventions are designed and scaled. In future work, employing a formal implementation science framework would further clarify how ST-informed digital interventions can be effectively deployed at scale.

## Data Availability

No datasets were generated or analysed during the current study.

## Abbreviations

G-BA: Gemeinsamer Bundesausschuss
GAD-2: Generalised Anxiety Disorder Questionnaire 2-Item
GDPR: General Data Protection Regulation
HOR: Head of Research
IQWiG: Institut für Qualität und Wirtschaftlichkeit im Gesundheitswesen
IPU: International Psychoanalytic University
K6: Kessler Psychological Distress Scale 6-Item
K10: Kessler Psychological Distress Scale 10-Item
MDBF: Mehrdimensionaler Befindlichkeitsfragebogen
MDMQ: Multidimensional Mood State Questionnaire
OSI: Online Self-help Intervention
PI: Principal Investigator
PHQ-4: Patient Health Questionnaire 4-Item
PSS-4: Perceived Stress Scale 4-Item
RCT: Randomised Controlled Trial
ST: Systemic Psychotherapy
UIC: Unique Identifying Code
UMUX-LITE: Two-item questionnaire based on the Usability Metric for User Experience (UMUX)
